## Abstract

**Background:**

Spinocerebellar ataxia type 3 (SCA3) is the most common subtype among the autosomal dominant cerebellar ataxias, a group of neurodegenerative disorders for which currently no disease-specific therapy is available. Evidence-based options for symptomatic treatment of ataxia are also limited. Recent investigations in a heterogeneous group of hereditary and acquired ataxias showed promising, prolonged effects of a two-week course with daily sessions of cerebellar anodal transcranial direct current stimulation (tDCS) on ataxia severity, gait speed, and upper limb dexterity. The aim of the SCA3-tDCS study is to further examine whether tDCS improves ataxia severity and various (cerebellar) non-motor symptoms in a homogeneous cohort of SCA3 patients and to explore the time course of these effects.

**Methods/design:**

An investigator-initiated, double-blind, randomized, sham-controlled, single-center trial will be conducted. Twenty mildly to moderately affected SCA3 patients (Scale for the Assessment and Rating of Ataxia score between 3 and 20) will be included and randomly assigned in a 1:1 ratio to either cerebellar anodal tDCS or sham cerebellar tDCS. Patients, investigators, and outcome assessors are unaware of treatment allocation. Cerebellar tDCS (20 min, 2 mA, ramp-up and down periods of 30 s each) will be delivered over ten sessions, distributed in two groups of five consecutive days with a two-day break in between. Outcomes are assessed after a single session of tDCS, after the tenth stimulation (T1), and after three, six, and twelve months. The primary outcome measure is the absolute change of the SARA score between baseline and T1. In addition, effects on a variety of other motor and neuropsychological functions in which the cerebellum is known to be involved will be evaluated using quantitative motor tests, static posturography, neurophysiological measurements, cognitive assessment, and questionnaires.

**Discussion:**

The results of this study will inform us whether repeated sessions of cerebellar anodal tDCS benefit SCA3 patients and whether this form of non-invasive stimulation might be a novel therapeutic approach to consider in a neurorehabilitation setting. Combined with two earlier controlled trials, a positive effect of the SCA3-tDCS study will encourage implementation of this intervention and stimulate further research in other SCAs and heredodegenerative ataxias.

**Trial registration:**

NL7321, registered October 8, 2018.

## Background

Spinocerebellar ataxia type 3 (SCA3) is the most common subtype among the autosomal dominant cerebellar ataxias (ADCAs), a clinically and genetically heterogeneous group of progressive neurodegenerative disorders [1–3]. Ataxia has been shown to be the primary and shared driver of both motor impairment and reduced quality of life in various SCAs [4, 5]. In addition to deterioration in the motor domain, specific cognitive abilities tend to decline and depressive symptoms frequently arise during disease progression [6–13].

As therapies that specifically target the underlying molecular and cellular processes are currently not available, SCA3 remains an untreatable condition and clinical management focuses on trying to provide symptomatic relief. Unfortunately, evidence-based options for symptomatic treatment of ataxia are still limited [14]. According to the recently published recommendations by the American Academy of Neurology [15], the only drug with class I study evidence of benefit in terms of improving ataxia in SCA patients is riluzole, although it should be noted that this particular trial did not include SCA3 patients [16]. In daily practice, training, exercise, and other rehabilitation programs compose the main pillars of intervention. These strategies might be beneficial, but previous research has shown that referrals to these facilities are inconsistent, ataxia-specific expertise in allied healthcare is limited, and guidelines are lacking [17]. Apart from the requirement to improve the organization of neurorehabilitation care, there is an urgent medical need to find alternative – or synergistic – ways to provide symptomatic relief for ataxia patients.

Cerebellar transcranial direct current stimulation (tDCS) is an increasingly used, safe, cheap, and non-invasive tool in neuroscience that is able to modulate cerebellar excitability [18, 19]. Computational modeling studies have demonstrated the biophysical feasibility of modulating cerebellar structures using tDCS with only negligible spreading effects to neighboring regions [20, 21]. Initially, this technique has been successfully applied in healthy volunteers to investigate the neural correlates of motor learning and cognitive and emotional processes [19, 22, 23]. More recently, studies also started to explore its therapeutic potential in a variety of neurological conditions [24, 25]. The first promising results of this technique in ataxia patients – significant reduction of upper limb postural and action tremor and dysmetria – have been described in single cases of SCA2 and ARCA3 due to *ANO10* gene mutations [26, 27]. These effects were subsequently corroborated on a larger scale by Benussi and colleagues in a randomized, double-blind, sham-controlled study enrolling a rather heterogeneous group of nineteen patients with both hereditary and acquired ataxias. Compared to the sham condition, a single session of anodal cerebellar tDCS resulted in a significant transient improvement in scores on the Scale for the Assessment and Rating of Ataxia (SARA), International Cooperative Ataxia Rating Scale (ICARS), 9-hole peg test (9HPT), and 8 m walk test (8MWT) [28]. Furthermore, a double-blind, randomized, sham-controlled trial by the same authors assessing the efficacy of tDCS five days per week for two consecutive weeks in a heterogeneous group of twenty ataxia patients – five SCA2, one SCA14, two SCA38, one Friedreich ataxia, one ataxia with oculomotor apraxia type 2, four multiple system atrophy cerebellar type, one fragile X-associated tremor/ataxia syndrome, and five sporadic adult-onset ataxia of unknown etiology – showed a significant improvement on all of the abovementioned scores up to three months after stimulation. This clinical amelioration was paralleled by restoration of the physiological inhibition of the pathways between the cerebellum and the contralateral motor cortex, as measured with double-coil transcranial magnetic stimulation (TMS) [29]. More specifically, this study was able to achieve a SARA score reduction of almost three points up to three months after stimulation, which would nearly equal the progression in SCA3 over two years [30]. Recently, these authors published the results of another randomized, double-blind, sham-controlled trial in twenty ataxia patients with mixed etiologies and found similar results regarding symptomatic ataxia improvement and return of cerebellar brain inhibition after ten sessions of cerebello-spinal tDCS [31]. No serious adverse events of cerebellar tDCS have been reported in these and other studies and it is therefore considered a safe and tolerable method. Possible side effects mainly include a transient itching, tingling, or mild burning sensation underneath the electrodes.

Inspired by these promising findings, we designed the clinically-oriented SCA3-tDCS study to investigate whether cerebellar anodal tDCS, compared to sham stimulation, decreases ataxia severity and a variety of (cerebellar) non-motor symptoms in a homogeneous cohort of SCA3 patients and if so, what the duration of this beneficial effect is.

## Methods/design

### Study design

The SCA3-tDCS study is an investigator-initiated, double-blind, randomized (1:1), sham-controlled, single-center trial that will take place at the Radboud University Medical Center, Nijmegen, the Netherlands. Cerebellar tDCS will be delivered during five consecutive days for two weeks, with a two-day break in between. Primary and secondary outcome measures (see Tables 1 and 2) are assessed at baseline (T0 before tDCS), after a single session of tDCS (T0 after tDCS), after the tenth session of tDCS (T1), and after three, six, and twelve months of follow-up (T2, T3, and T4, respectively). For this purpose, we will use a combined approach of a standardized neurological examination, quantitative motor tests, cognitive assessment, questionnaires, and neurophysiological measurements (Table 1). This combination of tests reflects the broad range of motor, cognitive, and affective functions the cerebellum is known to be involved in, and represents recognized domains of deficit in patients with cerebellar diseases.

**Table 1 Tab1:** Overview of the questionnaires, neurological tests, and kinetic and neurophysiological measurements at the various points in time of the SCA3-tDCS study

	T0 baseline	T0 after tDCS	T1 day 12	T2 3 months	T3 6 months	T4 12 months
Questionnaires						
EQ-5D-5L	X		X	X	X	X
PHQ-9	X		X	X	X	X
POMS 32-item	X		X	X	X	X
iMCQ	X					X
IPAQ parts 1 and 4	X			X		X
FARS part II (ADL)	X		X	X	X	X
Neurological examination						
CCAS scale	X		X	X	X	X
SARA	X	X	X	X	X	X
8MWT	X	X	X	X	X	X
9HPT	X	X	X	X	X	X
PATA repetition	X	X	X	X	X	X
INAS	X		X	X	X	X
Measurements						
TMS	X		X			
Delay EBC	X		X			
Static posturography	X	X	X			

*EQ-5D-5L* EuroQol 5-Dimension 5-Level, *PHQ-9* Patient Health Questionnaire-9, *POMS* Profile of Mood States, *iMCQ* Institute for Medical Technology Assessment (iMTA) Medical Consumption Questionnaire, *IPAQ* International Physical Activity Questionnaire; *FARS* Friedreich Ataxia Rating Scale, *ADL* Activities of Daily Living, *CCAS* Cerebellar Cognitive Affective Syndrome, *SARA* Scale for the Assessment and Rating of Ataxia, *8MWT* 8 m walk test, *9HPT* 9-hole peg test, *INAS* Inventory of Non-Ataxia Signs, *TMS* Transcranial magnetic stimulation, *EBC* Eyeblink conditioning

**Table 2 Tab2:** Outcome measures and tests

Outcome domain	Test	Time point
Primary outcome measure		
Cerebellar ataxia severity	SARA (absolute change from baseline)	T1
Secondary outcome measures		
Cerebellar ataxia severity	SARA (% of patients with a decrease of ≥ 1.5 points)	T1
Cerebellar ataxia severity	SARA score and subscores	T0 after tDCS, T2-T4
Gait speed	8 m walk test	T0 after tDCS, T1-T4
Articulation speed	PATA repetition rate	T0 after tDCS, T1-T4
Upper limb dexterity	9-hole peg test	T0 after tDCS, T1-T4
Extracerebellar signs	INAS count	T1-T4
Postural sway	Static posturography	T0 after tDCS and T1
Quality of life	EQ-5D-5L	T1-T4
Depression	PHQ-9	T1-T4
Mood states	POMS 32-item version	T1-T4
Cognition and affect	CCAS scale (total score and number of ‘fails’)	T1-T4
Activities of daily living	FARS part II	T1-T4
Medical consumption	iMCQ	T4
Motor learning	Delay EBC (acquisition of CRs)	T1
CBI	Transcranial magnetic stimulation	T1
tDCS-related side effects	Open question	T1
Correct randomization	Patients’ thoughts about treatment allocation	T1

*SARA* Scale for the Assessment and Rating of Ataxia, *INAS* Inventory of Non-Ataxia Signs, *EQ-5D-5L * EuroQol 5-Dimension 5-Level, *PHQ-9* Patient Health Questionnaire-9, *POMS* Profile of Mood States, *CCAS* Cerebellar Cognitive Affective Syndrome, *FARS* Friedreich Ataxia Rating Scale, i*MCQ* Institute for Medical Technology Assessment (iMTA) Medical Consumption Questionnaire, *EBC* Eyeblink conditioning; *CR* Conditioned response, *CBI* Cerebellar brain inhibition

The study has been registered in the Netherlands Trial Register (NL7321) on October 8, 2018, has been approved by the local medical ethics committee (CMO region Arnhem-Nijmegen), and will be conducted in accordance with the Declaration of Helsinki.

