#### Cerebellar transcranial direct current stimulation

Cerebellar tDCS will be delivered by two 7 × 5 cm rubber electrodes, which are connected to a neuroConn constant current stimulator. Similar to the set-up applied by Benussi and colleagues [29], the anode – encased in a dampened sponge envelope – will be placed in the midline 2 cm below the inion in order to reach both cerebellar hemispheres, while the cathode is attached to the skin overlying the right deltoid muscle. The anode and cathode are coated with electroconductive gel and paste, respectively, to maintain impedance levels below 5 kΩ throughout the stimulation. Elastic gauzes and tape are used to ensure fixation of the electrodes.

Following a ramp-up time of 30 s, as recommended previously to ensure proper blinding and reduce side effects [58], in which the current intensity is gradually increased from 0 to 2 mA, a maintenance current of 2 mA will be delivered for 20 min in case of real cerebellar stimulation (0.057 mA/cm^2^). Hereafter, the current is gradually decreased to 0 mA again during a fade-out period of 30 s. In sham sessions, the duration of real stimulation by convention is 40 s (i.e., 1200 / 30), directly preceded and followed by 30 s of ramp-up and ramp-down. The remainder of the time (i.e., 1160 s) consists of continuous impedance control without any stimulation. This is accomplished by the occurrence of a small current pulse every 550 ms (110 μA over 15 ms, peak current duration 3 ms) that enables reliable detection of bad electrode contact or disconnection. Both conditions will thus be indistinguishable with respect to electrode set-up, session duration, and physical sensations. After two weeks of stimulation, patients are asked to which group they think they were allocated.

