Participants may experience mild itching, prickling, or burning sensations underneath the electrodes that disappear after a while. Considering the extensive exclusion criteria, the screening procedure, and constant monitoring of the subjects, we do not expect serious adverse events. The risks of tDCS are considered negligible. No serious adverse events have been reported [23, 59] and the similar stimulation protocol used by the Italian group yielded no side effects [29]. In any case, the investigator will make sure that the stimulation is fully tolerable at the beginning as well as throughout the experiment. Measurements will be terminated whenever the participant does not tolerate the measurement or whenever the investigator believes it is not safe to proceed.

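### Table 2 measures side effects with one open question at T1, which suits transient sensations over ten sessions poorly and only weakly tests the claim that sham feels the same

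*Protocol article*

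**What the plan says.** In the protocol article, Table 2 (under Study design) has a secondary-outcome row for "tDCS-related side effects". The test is given as "Open question" and the time point as T1 only. T1 follows the last of the stimulations, which are "delivered over ten sessions, distributed in two groups of five consecutive days with a two-day break in between" (Abstract, Methods/design).

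The section on cerebellar transcranial direct current stimulation adds four relevant statements:

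- On what to expect: "Participants may experience mild itching, prickling, or burning sensations underneath the electrodes that disappear after a while". The Background likewise calls the possible side effects transient.
- On the sham: "Both conditions will thus be indistinguishable with respect to electrode set-up, session duration, and physical sensations".
- On oversight: "the investigator will make sure that the stimulation is fully tolerable at the beginning as well as throughout the experiment". The same paragraph refers to constant monitoring, but names no form, rating or recorded variable.
- On blinding: "After two weeks of stimulation, patients are asked to which group they think they were allocated". Table 2 lists this guess as a separate outcome at T1.

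**The concern.** The instrument and its timing do not fit what is being measured. The sensations are expected to fade and can recur over ten sessions, yet the outcome is one unprompted recollection at the end. It yields no session-level timing and no intensity, and some mild sensations may go unmentioned.

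Two uses of the data suffer. First, a low count of side effects would be hard to interpret, although the Discussion says a positive trial would point to a safe tool. Second, the claim that real and sham feel alike supports patient blinding, and the listed side-effect outcome is a blunt way to examine it. Patients' own expectation matters here because several secondary outcomes are self-reported (EQ-5D-5L, PHQ-9, POMS) and the motor tests depend on performance.

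**Working it through.** The article states no figure on this point, so there is none to reproduce. The check is mainly of the text.

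**1. Is T1 alone a deliberate choice?** Table 2 gives several time points where they are intended: gait speed, articulation and dexterity at T0 after tDCS and T1–T4; postural sway at T0 after tDCS and T1. Side effects have T1 only, and Table 1 has no side-effect row at any visit. Motor tests and posturography are repeated after the first session; side effects are not asked about then. No other section adds an instrument or a time point.

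**2. How far back must patients recall?** Five days + two days' break + five days = 12 days, which agrees with day 12 for T1 in Table 1. Taking the first session as day 1:

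- Sessions 1–5 (days 1–5) lie 12 − 5 = 7 to 12 − 1 = 11 days before T1.
- Sessions 6–10 (days 8–12) lie 12 − 12 = 0 to 12 − 8 = 4 days before T1.

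Half the sessions are recent; the other half are at least a week old.

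**3. Could the arms feel different?** Real stimulation holds 2 mA for 20 × 60 = 1200 s. Sham holds it for 1200 / 30 = 40 s, and the other 1200 − 40 = 1160 s carry only brief impedance pulses. Both have 30 s ramps. Onset is therefore matched, while time at full current differs 30-fold. If a sensation outlasts the sham current, the arms could differ in how long it is felt. The article does not say whether it does. Duration and intensity are the features that one open question at T1 is least able to capture.

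**4. How much can an arm comparison of occurrence show?** There are 10 patients per arm. I used a two-sided Fisher test at 0.05; the article does not state sidedness, and it names chi-square tests, but expected counts here are small.

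- 4/10 against 0/10: p = 2 × C(10,4) / C(20,4) = 2 × 210 / 4845 = 0.087.
- 5/10 against 0/10: p = 2 × C(10,5) / C(20,5) = 2 × 252 / 15504 = 0.033.

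So if nobody in one arm reports a side effect, at least 5 of 10 in the other must do so. Incomplete reporting weakens this further. To illustrate the direction, let true rates p1 and p2 be multiplied by the same reporting fraction q in both arms. Power is then the sum of Bin(a; 10, p1·q) × Bin(c; 10, p2·q) over all pairs (a, c) with Fisher p < 0.05.

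| Assumed true rates | q = 100% | 75% | 50% | 25% |
|---|---|---|---|---|
| 80% v 20% | 64% | 35% | 15% | 2% |
| 80% v 40% | 25% | 12% | 6% | 1% |

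All rates and fractions are assumptions, as the article gives none. The table shows direction only. It also shows that the comparison is limited even with complete reporting.

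**The case against.** The strongest case on the other side has five parts.

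- **The protocol already checks blinding.** The allocation guess at T1 picks up unblinding by any route, including sensations. This stands as a check on blinding overall, so a reader should not infer that unblinding would pass unseen. Nor does the article show that sensations are the main route to it. The guess does not measure sensations, however, and it comes after any benefit, so a correct guess cannot be traced to sensation rather than to perceived improvement.
- **SARA is rated from video by investigators blind to allocation and time point.** This stands for rater bias and limits the effect on the primary outcome. It does not address patient expectation.
- **Sessions are monitored.** A reader might infer that nothing is collected per session. A condensed article cannot support that, because a session log may exist in the full protocol. The point is confined to what Table 2 lists as the outcome.
- **Recall may be adequate.** Five sessions fall within the last five days, and a repeated sensation may well be remembered. Loss of timing and intensity is inherent in the method; loss of occurrence is possible but not shown.
- **Tolerability is not a stated objective and the study calls itself exploratory.** Both are true, and they bear on severity.

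A reader might also try to size the flaw by the upper confidence limit for no reports in 10 patients, by contrasting one record per patient with ten, or by multiplying an assumed incidence by an assumed recall. None of these works. The first reflects 10 patients per arm, which more frequent questioning leaves unchanged. The second treats repeated records on the same people as independent. The third has no source in the article.

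**Conclusion.** The point holds as a minor one. The article fixes a single open question at T1 for sensations that it describes as transient and that may arise in any of ten sessions. That outcome cannot give timing or intensity, may under-record occurrence, and is a weak test of the asserted equality of sensations between real and sham.

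The extent of under-recording cannot be sized from the article. The primary SARA analysis, its sample size and the power statement are unaffected. The conclusion assumes that Table 2 gives the side-effect outcome completely; if the full protocol lists a structured per-session sensation measure as an outcome, the point falls away once Table 2 is aligned with it.

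**What to change.** Change the Table 2 row to a short fixed list (itching, prickling, burning, other; each with intensity) plus the open question, completed by the patient after each of the ten sessions.

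- Have the patient fill it in, and keep it from the operator applying tDCS and from the outcome raters except where needed for safety. The Randomization and blinding section requires the operator to remain unaware of allocation, and a checklist run by the operator could supply cues.
- Report by arm, with the patient as the unit of analysis and sessions as repeated measures.
- Keep the allocation guess at T1.

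Patients already attend every session, so the cost is about a minute each time. The downsides are that prompting will raise reports of mild effects in both arms and may draw patients' attention to sensations. The change improves ascertainment, timing and intensity; it does not remove the limit set by 10 patients per arm.

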### Objectives

The primary objective of our study is to examine whether a two-week intervention with cerebellar anodal tDCS could lessen ataxia severity in SCA3 patients compared to sham stimulation. The secondary objectives are to investigate if a two-week treatment with cerebellar anodal tDCS (1) diminishes various (cerebellar) non-motor symptoms, (2) enhances the ability of SCA3 patients to acquire conditioned responses in a delay eyeblink classical conditioning paradigm, and (3) restores cerebellar brain inhibition pathways compared to sham stimulation. We will (4) also determine if a single session of tDCS has a transient beneficial effect on ataxia severity.

### Patient population and eligibility criteria

In order to be eligible to participate in this study, a subject must meet all of the following inclusion criteria:Age 16 years or older.Proven mutation in the *ATXN3* gene.SARA score between 3 and 20 at a recent (pre-study) visit. The SARA score reflects ataxia severity and ranges from 0 (no ataxia) to 40 (very severe ataxia) [32]. We previously distinguished between the asymptomatic, preclinical, and ataxic stage of SCAs and proposed definitions for each of these [33]. As about 20% of healthy controls in the SARA validation study were found to have positive ratings in at least one item, we defined clinically manifest ataxia as SARA ≥ 3 and this value will therefore be used as lower cut-off in the current trial. Further analysis of the results of the Benussi et al. study suggested that improvements following cerebellar anodal tDCS were greater in clinically less affected patients [29]. This indicates that a window of opportunity exists, probably related to the fact that in later stages of the disease there is severe neuronal loss and thus an absence of target cells to channel the tDCS effects. In this regard, Rubinsztein and Orr even speculate about a point of no return when a certain threshold of neurodegeneration has been exceeded and beyond which introduction of disease-modifying treatments may be futile [34]. In the current study, we therefore deliberately do not include SCA3 patients who are already wheelchair-bound but rather aim for mildly to moderately affected individuals, using an arbitrary SARA upper cut-off value of 20.

Exclusion criteria are:Epilepsy.History of brain surgery.Metallic implants in or near the skull.Presence of a pacemaker.Significant comorbidities that interfere with activities of daily life.(Suspicion of) pregnancy.Severe skin disease affecting the location where the tDCS electrodes will be placed.

Similar to the riluzole trial [16], we deliberately chose not to exclude patients who are receiving physical therapy or who are using centrally acting neurological medication, as we here plan to study the symptomatic effect of cerebellar tDCS added to any ongoing treatment reflecting current daily practice.

Patients will be mainly recruited from our Radboud University Medical Center ataxia outpatient clinic. If they are interested to participate, they will receive a detailed description of the study by post or e-mail and have at least seven days consideration time. In addition, the Dutch ADCA society will help in the recruitment by placing advertisements on their website and in their newsletter. Before enrollment, patients from other centers who are willing to participate are invited to our hospital for a pre-study visit in which the SARA score is determined.

